# SPACE FOR COPD delivered as a maintenance programme on pulmonary rehabilitation discharge: protocol of a randomised controlled trial evaluating the long-term effects on exercise tolerance and mental well-being

**DOI:** 10.1136/bmjopen-2021-055513

**Published:** 2022-04-25

**Keywords:** Protocols & guidelines, QUALITATIVE RESEARCH, REHABILITATION MEDICINE, RESPIRATORY MEDICINE (see Thoracic Medicine), Chronic airways disease

## Abstract

**Introduction:**

The benefits achieved during pulmonary rehabilitation (PR) are known to be sustained for 6–12 months after the initial programme. Several maintenance trials have been conducted but were heterogeneous in terms of duration, frequency and labour cost. There is no consensus on one best strategy. SPACE FOR COPD (Self-management Programme of Activity, Coping and Education for Chronic Obstructive Pulmonary Disease) is a home-based self-management programme, which has been shown previously to be effective in primary and secondary care settings and is to be tested here as a maintenance programme. The aim is to evaluate the efficacy of the SPACE FOR COPD programme (manual and group sessions), on exercise tolerance and mental well-being, compared with usual care following PR in patients with COPD.

**Methods and analysis:**

A prospective, multicentre, single-blinded randomised controlled trial requiring 116 participants with a clinical diagnosis of COPD who have finished PR within 4 weeks will be randomised 1:1 to either a usual care group or a SPACE FOR COPD programme group. The intervention comprises a home-based manual and 4, 2-hour group sessions adopting motivational interviewing techniques over 12 months. The primary outcome is endurance capacity measured by the Endurance Shuttle Walking Test at 12 months. Secondary outcomes are: maximal exercise capacity, health-related quality of life, mood, patient activation, physical activity, lung function and healthcare costs. The measures will be taken at baseline, 6 and 12 months. Patient interviews and staff focus groups will be conducted to explore barriers, facilitators and views about the intervention at the end of the study. A framework analysis will be used for the interpretation of qualitative data.

**Ethics and dissemination:**

The trial was granted ethical approval from Health Research Authority and Health and Care Research Wales (HCRW19/EM/0267 on 10 October 2019). Results will be made available to all stakeholders through a dissemination event, conferences and peer-reviewed publications.

**Trial registration number:**

ISRCTN30110012.

Strengths and limitations of this studyThis is a novel maintenance trial that uses an evidence-based home-based manual integrated with motivational interviewing skills to promote long-term self-management and behavioural change.Patients with chronic obstructive pulmonary disease who are registered in our patient and public involvement group were invited to review the protocol and two were involved in every aspect of developing the project.This is a multicentre trial, therefore the results may be more generalisable than a single centre.The programme is limited to English speakers only who can read at the level of an 8 year old. This may, therefore, exclude those who do not read in English or have low literacy.

## Introduction

To effectively manage chronic obstructive pulmonary disease (COPD), current national^1^ and international^2^ clinical guidelines recommend the addition of pulmonary rehabilitation (PR) to standard pharmacological therapy. PR is a non-pharmacological intervention known to help manage and improve respiratory symptoms in stable COPD conditions^3^ and is also recommended following a hospital admission for acute exacerbation of COPD.^1^ Moreover, PR is beneficial to improve exercise capacity,^3 4^ breathlessness,^3^ quality of life (QoL),^5^ anxiety and depression,^6^ and reduce healthcare utilisation.^7^ However, these benefits may only be sustained for 6–12 months after PR.^4^ A number of factors may affect the ability to maintain exercise capacity and QoL in the long term including: frequency of supervised maintenance exercise; strategies used to improve adherence to maintenance exercise; facilitators and barriers to long-term exercise training; and initial PR programme itself.^8^ Repeated exacerbations, progression of the disease and existence of co-morbidities may also have an impact^4^ Additionally, from a psychological perspective, patients with COPD report the feeling of abandonment after the graduation from PR as they lose the support from healthcare professionals (HCPs) and peers received during PR.^9^

Many interventions have been introduced to facilitate maintaining the benefits of PR beyond a 6–12 months period. Some of those studies revealed that maintenance interventions following PR is of benefit to COPD clients to maintain PR outcomes in the short term and long term (6–24 months).^10–12^ However, the interventions were heterogeneous in terms of duration, setting and level of supervision following initial PR. In addition, patients’ motivational and behaviour change strategies play a major role in maintenance but were examined in a limited numbers of the aforementioned maintenance interventions.^10–12^

Behaviour change can be supported using motivational interviewing (MI) techniques. MI is used to help coach people to make personal changes in their behaviour.^13^ MI has been shown to outperform traditional 'advice giving' in the treatment of a broad range of behavioural problems/diseases.^14^ To our knowledge, none of the previous maintenance interventions have used this technique per se. In COPD, MI coaching delivered on hospital discharge was shown to have a positive influence on readmissions and QoL compared with a control group.^15^

Incorporating an exercise manual with group sessions underpinned by MI techniques has been tested in primary and secondary settings as a home PR alternative compared with usual care^16^ and traditional (centre-based) PR.^17^ The studies revealed benefits in exercise performance, knowledge, anxiety and fatigue in which some of these outcomes were maintained 6 months after the initial delivery, when compared with usual care^16^ and non-inferior to PR.^16^ More recently, the programme has been delivered in groups to enhance peer support in COPD.^18^

Thus, for this trial, we propose a supervised maintenance package (Self-management Programme of Activity, Coping and Education FOR COPD, SPACE FOR COPD) with the aim of retaining the expected benefits of PR as well as increasing patients’ motivation and to address the feelings of abandonment following traditional PR. We will particularly focus on exacerbation and mood management, as well as promoting regular exercise in our programme. By developing this post PR intervention, we aim to preserve physical and mental well-being, potentially reducing the likelihood of repeat PR attendance and hospital readmissions. In this trial, we hypothesise that patients will have improvements in PR outcomes such as exercise capacity and overall QoL that will be maintained in the intervention group for at least 1 year. This also could be cost effective for the health service.

### Aims

The overarching aim of the study is to assess whether a self-management maintenance programme (SPACE FOR COPD), delivered on PR discharge, preserves the anticipated gains made in exercise tolerance and mental well-being at 12 months, compared with usual care alone.

The primary aim is:

To compare endurance walking distance at 12 months in those who have completed the SPACE FOR COPD maintenance programme compared with usual care.

The secondary aims are:

To compare the following variables at 12 months in patients who have completed the SPACE FOR COPD^©^ maintenance programme versus usual care:Maximum walking distance.QoL.Anxiety and depression.Physical activity.Symptoms (breathlessness, fatigue, sputum production, cough, sleep, chest tightness).Patient activation (knowledge, skills and confidence to manage COPD).Forced expiratory volume in 1 s.To measure adherence to the SPACE FOR COPD maintenance programme in terms of sessions attended, completion of the programme and manual diary entries.To collect data for future health economic analysis in both groups; including hospital admissions, healthcare contacts, personal social service costs and patientborne expenditure.To understand the patient experience of SPACE FOR COPD; to identify facilitators and barriers of the package to maintain health and well-being.To work with staff, managers and commissioners involved in the delivery of SPACE FOR COPD as a maintenance option to explore how, if successful, this programme could be rolled out more widely.To use data pre-PR, where available, to evaluate the effectiveness of the initial PR programme and its impact on the maintenance rehabilitation programmes outcomes.

## Methods and analysis

### Trial design and setting

The trial will be a prospective, multicentre, randomised controlled, single blind trial of SPACE FOR COPD maintenance programme vs usual care. There will be an integrated economic evaluation and also an embedded qualitative component. The trial will be conducted at two centres, the University Hospitals of Leicester (UHL) National Health Service (NHS) Trust in Leicester, UK, and Harefield Pulmonary Rehabilitation Unit, Harefield, UK. We have used the SPIRIT-2013 checklist and recommendations as a guide for designing this trial.^19^

The trial will consist of three visits (baseline, 6 and 12 months). Each visit will last for up to 2 hours where all outcomes will be collected. In addition, a 2-hour small group session will be conducted at month 1 after baseline visit then at months 4, 7 and 10 in the intervention group only (see figure 1). The trial recruitment will take place over 1 year, with a 1-year follow-up.

**Figure 1 F1:**
[figure not shown]
Study flow chart. SPACE FOR COPD, Self-management Programme of Activity, Coping and Education for Chronic Obstructive Pulmonary Disease. PA, Physical Activity

### Participants

#### Eligibility criteria for patients

Participants will be included if they meet the following criteria:

Completed PR within the last 4 weeks (PR must meet standards defined by the British Thoracic Society (BTS).^20^Clinical diagnosis of COPD.Able to read and write English to the age of an 8 year old.Eighteen years and older.

Participants will be excluded if they:

Have a significant disability which limits the daily physical activity.Unable to read and write English due to the nature of the manual’s language.

#### Eligibility criteria for HCPs

HCPs involved in delivering the intervention and will be invited to participate in focus groups. The inclusion criterion is to deliver one or more sessions. The aim is to explore their experience, the barriers and facilitators in delivering the group sessions. The HCPs are respiratory physiotherapists, respiratory nurses or health psychologists with experience in delivering PR. All involved HCPs have received MI training delivered by a health psychologist and introduction on how to deliver the group sessions using a dedicated trial manual.

### Procedure

#### Usual care (control group)

The control group will receive usual care: written maintenance advice as recommended by the BTS quality standards.^21^ Leaflets will be given to signpost the individual to maintenance options for exercise following PR. A referral to community exercise schemes will be arranged for the control and intervention groups, if available or desired, as this represents best usual care across the UK.

#### Space for COPD maintenance programme (intervention group)

Participants in the intervention group will receive the SPACE FOR COPD home-based maintenance programme manual and be invited to attend SPACE FOR COPD group-based maintenance sessions detailed below.

#### Space for COPD home-based manual

Precise details of the rationale, development and efficacy of the work underpinning the SPACE FOR COPD manual are available elsewhere.^22^ The manual is divided into four stages providing an exercise programme and covering educational topics. It includes self-management skills, disease specific information and tasks. The content of the manual has been approved by the Plain English Campaign and received the Crystal Mark for Clarity of British English. The content of the manual is outlined in table 1. Table 2 demonstrates the mapping of self-management components of the manual to the PRISMS taxonomy framework. There is a COPD action plan insert which is consistent with the recruiting centres’ usual care.

**Table 1 T1:** Manual components

Stage 1	Stage 4
What’s happened to your lungs?	Staying fit and your hobbies
Exercise: How to get fitter	Your relationships
Setting your goals	Dealing with setbacks
Managing your stress - part 1	Sex and your lungs
Your emotions	Breathe easy
Controlling your breathing	Conclusion
Information about your medication	
Stage 2	Frequently Asked Questions (FAQs) and appendix
How to stay fit	Frequently asked questions
Managing days when you feel unwell	Setting your walking speed
Saving your energy	Help for carers
Diet and feeling unwell	Advice about oxygen
Advice for clearing your chest	Smoking: advice on giving up
Stage 3	Cleaning your breathing devices
How to get stronger	Spare walking diaries
Managing your stress—part 2	Spare strength training diaries
Healthy eating	
Travelling and your lung disease	

**Table 2 T2:** Practical Reviews in Self-Management Support (PRISMS) taxonomy components and examples in the manual

PRISMS taxonomy component	Elaboration	Examples from the SPACE FOR COPD facilitator manual
Information about condition and/ or its management	Specific information about COPD is provided within the Stage 1 of the manual.	Participants are provided with information throughout the programme (every session)
Information about available resources		Participants are provided with information throughout the programme (every session)
Provision of/agreement on specific clinical action plans and/or rescue medication	COPD Action Plan is included as an insert in the manual	Actions plans in session 2
Practical support with adherence (medication or behavioural)	Walking and strength training diaries are provided for participants and discussed during sessions	Walking and strength training diaries are provided for participants and discussed during solution focused goal feedback at the beginning of sessions 2, 3 and 4
Provision of easy access to advice or support when needed	Participants are able to call programme facilitators between sessions with questions	Participants are provided with contact details for programme facilitators who the can call if needed (throughout programme).
Training/rehearsal for practical self-management activities	Including: Managing exacerbations Saving your energy	Session two covers managing exacerbations Session three covers saving your energy
Training/rehearsal for psychological strategies	Including: Goal setting Solution focused goal feedback Problem solving Self-reward and social reward Managing stress and emotions	Goal setting activity (including action planning) and solution focused goal feedback (once every session). Problem solving (throughout programme) Managing stress and emotions in session 3.
Social support	Including: Practical support Emotional support Peer support Group socialising is encouraged	Participants are encouraged to share experiences, advice, ideas and support each other (throughout the programme).
Lifestyle advice and support	Including: Introduction to the walking programme Strength training Hobbies Maintaining exercise	Introduction to walking programme in session 1 Hobbies (session 3) Maintaining exercise (session 4)

SPACE FOR COPD, Self-management Programme of Activity, Coping and Education for Chronic Obstructive Pulmonary Disease.

For the purpose of this trial, a new single page insert has been developed to facilitate longer term goal setting by following the Specific, Measurable, Achievable, Relevant and Time bound method for goal settings. HCPs will advise participants on how to use and follow the manual independently at home. Participants will also be asked to complete section of the manual at home (eg, exercise diaries) and will have the opportunity to call HCPs with questions via telephone.

#### Group sessions

The group sessions are held in small groups (5–10 participants per group) that will accompany the SPACE FOR COPD maintenance programme manual with the aim of discussing progress, addressing barriers, increasing motivation to maintenance, to enhance health lifestyle behaviours and to encourage social support. The content of these sessions is shown in figure 2. HCPs facilitating the groups will use MI techniques to identify barriers and facilitators to maintaining exercise, expressing empathy, supporting self-efficacy and ‘rolling with resistance’. Group sessions will be facilitated by two HCPs (eg, Physiotherapists, respiratory specialist nurses, health psychologists). There will be four sessions every 3 months over the period of 1 year.

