**Figure 2 F2:**
[figure not shown]
Group sessions contents. SPACE FOR, COPD, Self-management Programme of Activity, Coping and Education for Chronic Obstructive Pulmonary Disease.

We anticipate that some participants may not be able to attend all the group sessions or may be unable or unwilling to attend the research centre. In this instance, we will accommodate the participant in another session (with permission of that group) or via videoconferencing. If this isn’t possible a telephone contact will be conducted instead.

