### Data analysis

#### Quantitative analysis

All data will be analysed on an intention-to-treat basis using SPSS software (V.26.0, IBM). We will conduct a separate per-protocol analysis for those who complete the intervention. Continuous variables will be presented as mean (SD), categorical variables as frequencies (percentages). All data will be assessed for outliers, normality and analysed using appropriate parametric and non-parametric statistics. To test the primary outcome, the difference between the two groups for the ESWT time will be analysed at 12 months using an independent t-test (or non-parametric equivalent).

Secondary outcome measures will be analysed in the same way. We will also look at changes in all outcomes in individual participants over time (ie, pre-PR, post-PR, 6 months and 12 months) using a repeated measures analysis of variance (or non-parametric alternative). Significance will be set at p<0.05 and differences between groups will be expressed as mean (95% CIs). Analysis will take into account the baseline values and adjust for potential confounders (eg, age, disease severity). Missing data will be corrected for by multiple imputation. Interim data may be made available for abstracts but unmasking will not occur.

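### The intervention is delivered in groups in one arm only, but the named t-test treats all patients as independent; if outcomes correlate within group, its standard error is too small

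*Protocol article*

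**What the plan says.** **Delivery.** The Group sessions section states: "The group sessions are held in small groups", with 5–10 patients in each. It adds: "Group sessions will be facilitated by two HCPs". Trial design and setting places the sessions at month 1, "then at months 4, 7 and 10 in the intervention group only". Controls receive written advice and signposting leaflets (Usual care). Both arms may be referred to community exercise schemes.

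**Intended influence within groups.** The social-support row of Table 2 reads: "Participants are encouraged to share experiences, advice, ideas and support each other (throughout the programme".

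**Movement between groups.** For patients who cannot attend, the paragraph after Figure 2 says "we will accommodate the participant in another session (with permission of that group) or via videoconferencing", with a telephone contact as the last resort. Patient adherence repeats this and adds one-to-one contact.

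**Analysis.** Quantitative analysis says that "the ESWT time will be analysed at 12 months using an independent t-test (or non-parametric equivalent". Secondary outcomes follow the same approach. The only adjustments named are for baseline and for confounders such as age and disease severity.

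**Sample size.** The paragraph asks for 116 patients for 80% power to detect 184 s (SD 282 s) at the 5% level, including 20% attrition. It mentions no ICC, design effect or session group.

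**The concern.** Intervention patients in one group share two facilitators, a set of peers and four sessions over a year, and peer support is meant to be part of the effect. Controls have no such grouping. This is a partially nested design. A t-test, or a rank test in its place, assumes that every patient is independent in both arms. Adjusting for baseline, age or severity does not restore independence, because the shared influence arises after randomisation.

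If groups differ in how much they benefit, the intervention mean varies more than the patient-level SD implies. The primary confidence interval is then too narrow and the nominal 5% is exceeded. The secondary outcomes inherit this, including mood and patient activation, which group support addresses directly.

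The article names the test, so the choice has not simply been left to a later analysis plan.

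**Working it through.** **Inputs from the protocol article.** Difference 184 s, SD 282 s, 5% level (two-sided assumed), 80% power, 116 patients, 20% attrition (Sample size); 1:1 allocation (Randomisation and blinding); groups of 5–10 (Group sessions). **Assumed, not in the documents:** ICC 0.02, 0.05 and 0.10.

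**1. The plan's own figure.** n per arm = 2 × (1.960 + 0.842)² × 282² / 184² = 36.9, so 37 (38 with the exact t). Dividing by 0.8 gives 47–48 per arm, or 94–96 in total. The stated 116 does not follow from these inputs. That is a separate matter, but it means 116 is about 20 more than independence requires.

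**2. Groups and analysed size.** 116 / 2 = 58 per arm. 58/10 to 58/5 is about 6 to 12 groups. After 20% loss, 58 × 0.8 is about 46 per arm, so analysed group size m = 46/k runs from 7.7 (k = 6) to 3.8 (k = 12).

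**3. Type I error of the unadjusted t-test.** Design effect in the intervention arm: DE = 1 + (m − 1) × ICC. True SE divided by the t-test's SE: r = √((1 + DE)/2). Type I error = 2 × (1 − Φ(1.96/r)).

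Example, k = 6, ICC 0.05: DE = 1 + 6.67 × 0.05 = 1.333; r = √(2.333/2) = 1.080; type I error = 7.0%.

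| Groups (m) | ICC 0.02 | ICC 0.05 | ICC 0.10 |
|---|---|---|---|
| 6 (7.7) | 5.8% | 7.0% | 9.0% |
| 8 (5.8) | 5.6% | 6.4% | 7.8% |
| 12 (3.8) | 5.3% | 5.8% | 6.7% |

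Simulating the t-test with 46 per arm (40,000 runs per cell) gave 5.5%, 7.2% and 9.1% for 6 groups; 5.5%, 6.2% and 7.8% for 8; and 5.3%, 5.8% and 6.7% for 12. At ICC 0 it gave 4.8–5.0%.

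**4. Power for 116 with a correct standard error.** Under independence, 46 per arm gives 87–88%. With clustering, V₁ = 282² × DE/46 and V₀ = 282²/46. Approximate Satterthwaite df = (V₁ + V₀)² / (V₁²/(k − 1) + V₀²/45). Power comes from the non-central t with non-centrality 184/√(V₁ + V₀). At ICC 0.05:

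| Groups | DE | SE (s) | df | Power, normal approximation | Power, small-sample df |
|---|---|---|---|---|---|
| 6 | 1.333 | 63.5 | 14.4 | 82.6% | 77.0% |
| 8 | 1.238 | 62.2 | 20.8 | 84.1% | 80.5% |
| 12 | 1.142 | 60.8 | 32.6 | 85.6% | 83.5% |

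The small-sample figures move by up to about one point with the approximation used for the degrees of freedom, so 76–77% is a fair statement for 6 groups.

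**The case against.** **No ICC is given, and clustering may be weak.** Contact is four 2-hour sessions in a year, alongside a manual used at home. Absentees may join another group, a video link, a telephone call or a one-to-one contact. Delivery is standardised through shared training, a facilitator manual, cross-site teleconferences and fidelity checklists (Staff training and intervention fidelity). The endpoint is a walking test scored by a blinded assessor. All of this stands as reason to expect a modest ICC, but it does not show that the ICC is zero. The alternatives are fallbacks for patients who cannot attend, and peer influence is intended.

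**Under a strict null there is nothing to cluster.** If the programme affects nobody, the sessions cannot create correlation in one arm. Influences of site or calendar time reach controls too. This is correct: excess false positives require some groups to gain and others to lose, averaging to zero. It does not rescue the confidence interval, which is too narrow whenever benefit varies by group.

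**A reader might infer that type I error certainly exceeds 5%, or reaches 10%.** The documents do not support either. The first needs ICC above zero. The second needs ICC 0.10 with groups still at 10 after attrition (DE = 1.90, r = 1.204, 10.4%), whereas 46 analysed patients in 6 groups average 7.7.

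**A reader might also infer that the trial is too small.** The margin of 116 over 94–96 absorbs modest clustering. By the normal approximation with 46 per arm, power stays at 80% up to an ICC of about 0.12 at group size 5, or 0.055 at size 10. Small-sample degrees of freedom use up some of that margin, but only under an assumed ICC.

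**Conclusion.** The concern holds in conditional form. The article fixes a primary test that ignores grouping present in one arm only. If the within-group ICC is above zero, the standard error is too small and type I error is above 5%: about 5–6% at ICC 0.02, 6–7% at 0.05 and 7–9% at 0.10. These figures assume 46 analysed per arm, 6 to 12 equal groups, equal total variance in the two arms and stable group membership. Movement between groups and remote contact would reduce them.

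No shortfall in the stated 80% power is established. What the sample-size paragraph lacks is a stated clustering assumption, not a demonstrated number of patients. The matter should be corrected, but it does not by itself undermine the trial.

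**What to change.** 1. Record the first-assigned session group for every intervention patient, and keep that label even if the patient later attends another group or is contacted remotely.
2. Replace the t-test for ESWT with a partially nested linear mixed model: arm and baseline ESWT as fixed effects, a random intercept for session group in the intervention arm only, controls as singletons, and Satterthwaite or Kenward–Roger degrees of freedom. Treat the secondary outcomes alike.
3. Report the estimated ICC with the primary result.
4. In the sample-size paragraph, state the assumed ICC and number of groups, and the power for 116 computed with the same degrees of freedom. At ICC 0.05 this is about 76–77% with 6 groups, 80–81% with 8 and 83% with 12. A normal-approximation figure should not be quoted beside a small-sample analysis.

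The cost is one extra data field and revised analysis wording, with no extra patients. The confidence interval will be wider, more so with few groups, and the group variance will be estimated imprecisely.
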